# Background and rationale:

## Context of the study:

This document describes an updated protocol for study 1.2 in the original ACT Consortium Protocol (“An examination of ACT strategy in south-central Asia on falciparum malaria in a context where vivax is the major species”). The ACTc Programme in Afghanistan has been running since 2008 in two provinces, Kunduz in the North (run by Merlin) and Nangahar in the East (run by HealthNet TPO). The study aims to examine the effectiveness of different diagnostic strategies for improving targeting of antimalarial drugs.

Since the drafting of the original concept for study 1.2 (Cluster randomised study), three significant policy and operational changes have occurred in the study areas.

- Implementation of new microscopy centres (in Kunduz province).
- Large scale distribution of ITNs in the study provinces
- The planned implementation of a large national programme to scale up access to diagnostics at community and clinic levels.

These changes have had a significant effect on the policy and operational setting of the project and have changed the overall strategy of this stage of the programme. Firstly, additional clinics both in the study areas and elsewhere will be provided with microscopy and/or RDTs for diagnostics and ITNs will have been widely distributed in the study areas including most households. More significantly, a program to deliver RDTs for malaria diagnosis through 150 health posts staffed by Community Health Workers in endemic areas began this year.

The ACTc programme has examined the effectiveness of RDTs for targeting antimalarial drugs at the primary clinic level by measuring the accuracy of treatment under different diagnostic conditions. Microscopic (both established and new), clinical (i.e. non-parasitological) diagnosis and RDTs have been compared using a randomised trial design. Results of these surveys are forthcoming and will provide data on the implementation of diagnostics at the clinic level. In view of the forthcoming policy change to deliver RDTs at the community level through networks of community health workers, this protocol describes a plan for evaluating the effectiveness of RDT delivery at community level in targeting of antimalarial drugs.

## Scientific Rationale:

Targeting of antimalarial drugs is an important priority for delivery of effective treatments and requires parasitological diagnosis of malaria parasites and prescription of appropriate treatment. In areas where cases result from two or more species (typically *Plasmodium falciparum* and *P. vivax*) treatments for the two species differ. Because falciparum malaria has developed resistance to chloroquine, which remains effective against vivax malaria, identification of the species of malaria is vital for targeting ACTs.

Most malaria in Afghanistan is caused by vivax, which is a minority (although significant) cause of febrile illness. A few (around 5-10%) of cases are caused by falciparum malaria, which is treated with more expensive artemisinin combination therapy drugs (ACT). Identifying these few cases of falciparum and targeting the more expensive drugs at the few cases that occur is the major challenge. Mistreatment of falciparum as vivax (i.e. with chloroquine) could lead to poor treatment outcomes, where vivax treated as falciparum (i.e. with the more expensive ACT drugs) wastes expensive drugs. This places great importance on access to accurate diagnosis that can distinguish between the species.

Current research conducted at clinic basic health centre level shows that when parasitological diagnosis (using either RDTs or microscopy) is implemented at the clinic level, there is an improvement in treatment accuracy (i.e. the proportion of patients who are correctly treated) when compared to clinical diagnosis only (i.e. where there is no identification of parasites). However, despite this improvement around 50% of patients who are negative for malaria parasites are still treated with antimalarial drugs. The research conclusions show that improving the targeting of drugs requires not only the implementation of parasitological diagnosis, but also a change in prescriber behaviour. The over treatment for malaria, despite negative laboratory results, wastes drugs, reduces the cost-effectiveness of the diagnostic method, and (most importantly) leads to mistreatment of other causes of fever.

While the rollout of RDTs at clinic level has some evidence base (in part, from the previous ACTc studies), there is little available data on the effectiveness with which this intervention can be provided at community level through CHWs. The data that does exist locally is based on two studies, one conducted in 2006^[[1]](#footnote-1)^ and one ongoing pilot programme^[[2]](#footnote-2)^. Evidence from the study and from the pilot programme suggests that RDTs are not utilised effectively by CHWs. In the study, high rates of invalid tests were reported due to user error, and in both programmes, RDTs are incorrectly applied to patient’s symptoms. The results are that very large numbers of RDTs are used, and very few cases of malaria are adequately detected. The effect of RDTs on treatment decisions and accuracy was not noted by either study.

Use of RDTs at community level will also have an effect on current guidelines for management of febrile illness and diseases of children. The current community IMCI guidelines for Afghanistan (and most of Asia) do not include RDTs in the differential diagnosis of childhood diseases in the community. The current guidelines favour a blanket approach to treatment of “suspected malaria” where there is no other obvious cause of illness and the patient is in an endemic area. Changing these guidelines requires an evidence based approach to assess both the clinical and economic aspects of the intervention – something which has thus far not been conducted despite the trend in programming which has now started to deploy RDTs much more widely.

This study aims to provide evidence on the effectiveness of RDTs that have been deployed at community level by measuring the accuracy of the tests themselves, and the accuracy with which treatment is provided to malaria positive and malaria negative cases.

# Study Design and Methods:

## Study Objectives:

Primary Objective: To assess the effectiveness of deployment of malaria rapid diagnostic tests by Community Health Workers for improving access and targeting of antimalarial drugs in Afghanistan using a cluster randomised intervention study in two phases.

Secondary Objectives:

- To assess the current role of Community Health Workers in the treatment of fever (as defined by the CHW).
- To assess the effect of RDT implementation amongst community health workers on accuracy and timing of treatment in patients presenting with fever.
- To assess the effect of RDTs on the treatment of children presenting with fever at community level.
- To assess a package of interventions that aims to improve treatment targeting by community health workers.
- To examine the cost effectiveness of each intervention.
- To examine the effect of RDT on provider and user behaviour using qualitative methods.
- To make recommendations for policies which can improve community based health programmes (for example, IMCI).

## Study Sites and Patient Enrolment:

- - 1. *Clinics:* The study will be conducted using 22 clinics which have previously been used for ACT Consortium research. Twelve clinics are situated in Nanagahar Province (East Region) and ten clinics are based in Kunduz Province (North Region). The study areas have varying malaria endemicity, with higher incidence in the East Region. All clinics have been included as study sites for the previous phases of the project and are included in this study as a representative sample of typical clinics in different malaria endemic areas. The clinics are all primary care clinics (Basic Health Centre or Comprehensive Health Centre). They are staffed by a clinic doctor, who acts as the manager, and other staff (for example, nurses or midwives) who occasionally run the clinic when the doctor is away from post. Each centre also has a community health supervisor, who is responsible for the community health workers attached to each clinic.

## *Number of Health-posts per clinic:* Amongst the 22 clinics, there are 196 health posts, with 65 in Kunduz and 142 in Nangahar (table).

| **Province/clinic** | **Number of Health Posts** |
| --- | --- |
| **Kunduz** | **65** |
| Ajighan | 6 |
| AngorBagh | 7 |
| ArbabRamazani | 2 |
| BolaQachi | 5 |
| CharSari | 6 |
| Khan Abad | 20 |
| KhwajaGhaltan | 8 |
| Madrasa | 3 |
| Nick Pay | 3 |
| SandoqSai | 5 |
| **Nangarhar** | **142** |
| Baro | 8 |
| Batikot | 21 |
| Behsood | 16 |
| Chardhi | 6 |
| GardiGhos | 6 |
| Khewa | 12 |
| LandaBuch | 10 |
| MamandDara | 11 |
| NajmulQura | 6 |
| Rodat | 13 |
| SangarSarai | 18 |
| Shegay | 15 |
| **Grand Total** | **207** |

Each health-post has two staff – one female and one male CHW who will be enrolling patients into the study.

- - 1. *Health System at Community level:* The clinics act as a base for community based interventions. Community interventions are provided through a network of community health workers (CHWs) (for which community midwives are also included in some areas). The CHWs are administratively attached to a single clinic and are supervised by the Community Health Supervisor (CHS). There are between 3 and 10 CHWs attached to each clinic, depending on the catchment area or population of the clinics. CHWs operate within their communities, from their homes (called Health Posts). CHWs are volunteers who are selected by the communities they serve. They have numerous roles within the health system, including:
- Acute care and first-aid (including IMCI)
- Delivery of EPI and polio vaccine
- Delivery of insecticide treated nets
- Health education and awareness
- Attendance at trainings
- Health Information and Management data reporting
- Midwifery services (community midwives)

Typically, CHWs have had general training as well as multiple other trainings conducted by individual programmes (for example, the National Malaria Control Programme, EPI). They may be semiliterate, or illiterate, and have varying levels of training.

## Pre-study CHW data:

*Pre-study interviews:*

Data collected from all CHWs using a basic information form filled out at start of pre-study period (annex 1 for form):

- Personal data
- HP name/number
- Educational background / literacy
- Work history (last 3 years?)
- Current job other than a CHW
- GPS coordinates of the HP (if feasible), if not estimated distance to the mother-clinic.
- Length of time living in the village / area
- Socio-economic background / status

At this stage, the CHW will be assigned a CHW number (e.g. cNBA/01). Newly enrolled CHWs (i.e. for replacements) will be assigned the next sequential number on the list (e.g. cNBA/07).

## Post-intervention evaluation of CHW Practice:

At the end of phase 1 (and repeated at the end of phase 2), an evaluation will examine the current practice of CHWs in diagnosis, treatment and referral of malaria cases. The objective is to describe differences in practice between the two arms of the trial.

Secondly the post-intervention study will use structured observational studies (using a checklist), semi-structured interviews with the CHWs, their community health supervisor (CHS) and others involved in CHW task scheduling, and review of programme records on the activities of CHWs who will be included in the study. This will provide information on current practices, standards, quality and deficiencies (Annex 1).

The study will establish indicators and potential explanatory variables through interviews, observation and review of programme records, with the primary comparison being between the two intervention arms:

Review of Programme Records:

- Number of CHW activities per month for each HP attached to our trial clinics over the trial length.
- Type of activity (proportion health education, preventative, consultations)
- Age range of patients seen by CHWs
- Location of activities (travel log) – primary data spanning 1 typical month
- Number of consultations per week with reasons for each (e.g. malaria, URTI, distribution of condoms, etc)
- CHW supervisory visits by CHSs and visits by CHWs to CHSs (frequency, what tools are used during these visits, feedback mechanisms) – previous month (May 2011 – AFG Calendar)

Data collected from a sub-group for more detailed interviews, stratified by province, gender and clinic type (CHC vs. BHC) (Soc Sci Officers).

- Current CHW practice where malaria is suspected, using case studies and in depth interview techniques – primary interview in random subsample.
- Motivation for the job
- Time per activity data – pre and during the trial (at end of phase 1) over 1 week
- Knowledge of malaria, fever, IMCI, and blood safety
- Current CHW IMCI practice using case studies and in depth interviews
- Current CHW referral practice (under what clinical circumstances and how many per week)CHW drug stock (types, quantity, expiry dates, storage conditions)
- CHW re-stock procedure (via interview if it does not occur during observation)
- CHW job-aids and reporting templates (types provided, how they are used)
- CHW basic training (description of what is covered) and any further training given
- CHW literacy and pre-training education level
- CHW day job (any paid employment that is normally undertaken).
- CHW schedule (as prescribed by BPHS implementer and CHS)
- Motivation and personal factors influencing their roles as CHWs

The study will also examine supervisory and community structures by interview and focus groups with Community Health Supervisors and community members/leaders.

At the end of phase 1 and end of phase II of the trial (see next section), a series of social science assessments will be conducted.

In-depth interviews will be conducted with a purposive sample of CHWs, to be conducted after phase 1 of the trial.  The CHWs will be divided into groups according to how they responded to the trial; group A will be "controls" who dealt with the patient appropriately (selected for diagnosis, interpreted RDT, treated, referred) and other groups as needed who did not deal with the patient appropriately.  These groups will be defined by the "problem responses" of CHWs that come up in the data; for example if all CHWs select patients for diagnosis with an RDT correctly and refer correctly but do not treat according to the RDT results correctly, then the CHWs who did not treat correctly will form group B.  Approximately 5 CHWs will need to be interviewed from each group, for each arm.  Responses will be compared between arms.  Topic guides for these CHW IDIs will be developed as the trial progresses and information collected which can guide the development of the guides.

In-depth interviews to be conducted with a purposive selection of patients, during phase 1 of the trial. The interviews will be used to identify, in general, the patient perspectives of CHW services, what they use them for and when, as well as whether there has been any change in their perceptions of these services since the start of the trial (re introduction of RDTs etc).  For the latter question, patient IDIs from both arms will be compared.  Approximately 10 patients will be selected from each arm.  Again, topic guides will be developed during the trial.

Focus group discussions to be held with community leaders after phase 1 of the trial.  The purpose is as for patient IDIs above, to determine their perceptions of CHW services and note any changes since trial.  Approximately 3 community leaders will be selected per arm (i.e. 2 focus group discussions).  Again, topic guides will be developed during the trial.

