### Trial Arms:

**Phase I:**

*Arm 1: Non-intervention arm:*

The non-intervention arm will be based on the existing clinical diagnosis, pre-referral treatment and referral to a clinic in areas where RDTs have not been deployed at CHW level. Arm 1 CHWs will receive refresher training according to the National Strategy for CBMM which includes the current IMCI guidelines.

Vs:

*Arm 2: RDT Arm*

Provision of community level diagnostics by rolling out RDTs to CHWs through the national strategy for Community based Management of Malaria. The arm has been designed exactly as the current National guidelines for RDT implementation..The arm will include:

- Clinic level microscopy or RDT and CHWs using RDTs to provide parasitological diagnosis to diagnose, treat and/or refer patients. Under this scheme, CHWs will be provided with CQ, SP and artesunate (AS). Depending on the diagnostic result, they prescribe according to the National Treatment Guidelines (CQ for confirmed vivax, SP and AS for confirmed falciparum, and no antimalarial for a negative result).
- CHW training will be conducted exactly as described in the CBMM strategy, using a “trickle down approach” where Training of Trainers takes place at the central level for provincial trainers of local NGOS who run the health service. These, in turn, run workshops for training CHSs and CHWs (see section 2.2 for pre-evaluation of training and roll-out). Participants will receive training to enforce revised IMCI guidelines, taken from the CBMM strategy document, which include an RDT in the algorithm for fever (see annex 2).
- There are no plans for additional support or refresher training, and no plans for quality control and assurance contained in the National Plan.
- CHWs are not equipped with suitable storage facilities for the RDTs, for example evaporative coolers.
- Monitoring and evaluation takes place according to the draft strategy.

The second phase of the trial will be initiated in Feb 2012. The second phase of the trial will re-randomise clinics to either the RDT arm (as in arm 2, above) and a third arm (arm 3). The third arm will answer the question: “how can the performance of RDTs at community level be enhanced?”. The same set of outcomes will be used to measure the relative effectiveness of each approach. A revised random allocation using the same methods will be conducted for the Phase II randomisation.

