### Balance criteria:

The following variables that are expected to be important correlates of the primary outcome and on which we wish to achieve balance were based on a data collected in 2009 in the same study clusters and over the same study period i.e. July to December.

1. Harmonic mean. For a given number of clusters and overall sample size maximum statistical efficiency is obtained if an equal number of patients per cluster are selected. The total sample size of 1500 across 22 clusters would require an *arithmetic* mean of 68 patients per cluster. However, due to the huge variability in the proportion of patients seen with suspected diarrhoea, URTI and malaria (when CHWs are likely to use RDTs) per cluster this approach was not seen as appropriate for several reasons including time to reach sample size quota, and cluster representation. Hence the sample size was weighted according to the cluster proportion of patients seen with suspected diarrhoea, URTI and malaria to achieve a *harmonic* mean of 68 patients per cluster in each arm. Since the sample size calculation was done before randomisation the overall harmonic mean (for all clusters) was used but this does not guarantee a harmonic mean of 68 per arm and therefore this was included as a restriction factor in the randomisation.
2. Total sample size. The precision and power of a study are usually maximised when sample sizes are similar in the treatment arms. In CRTs this means that the number of clusters as well as the number of individuals should be similar across treatment arms. Therefore, due to the variability in sample size per cluster this was also added as a restriction factor.
3. Number of health posts. There is a substantial amount of variation in the number of health posts per cluster from 2 to 26. Clusters (clinics) with bigger catchment populations have more health posts and therefore by balancing on this factor and equal sample size per arm will be achieved.

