**Figure 2: Phase 2 trial schematic.**

### Case definition and patient enrolment:

Patients will be drawn from the communities where the CHWs operate and the clinics which supervise and support those CHWs. Inclusion criteria will be:

- Any patient where the CHW* or clinician considers malaria in the diagnosis – either prescribing an antimalarial or would request a malaria test if available or referring for diagnosis of malaria elsewhere.
- Patient, or parent/guardian, gives informed consent to the study.

*any community health worker who consults with patients and prescribes treatment, and is administratively attached to one of the study clinics.

Exclusion criteria will be

- Patients with a diagnostic result from another facility.
- Patients referred on for diagnosis in the private sector.
- Patients who have signs of severe or complicated disease and are referred prior to giving any diagnosis using the interventions.

Patients can be enrolled during any consultation with a CHW no matter where it takes place. The consultation could be made at the health post, the patient’s residence, or even outside in the street or fields. The CHW will also use the standard national HMIS tool for recording all their consultations, which will also allow assessment of any changes to practice within the community by identifying changes in the number of each type of consultation (for example, community DOTS, health awareness, condom distribution, etc).

If the patient gives informed consent, the CHW will assign a unique patient number and note the patients information on a pro-forma pictorial record form (Patient Tracking Form, see section 2.6). The patient tracking form has been designed for semi literate and illiterate health workers and has been pretested and validation in field testing using CHWs in Nangahar province.

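### The end-of-phase evaluation takes its supervisory-visit records from May 2011, before either phase, so those records can show only pre-intervention differences between arms

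*Protocol*

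**What the plan says.** Protocol section 2.4 sets the timing: "At the end of phase 1 (and repeated at the end of phase 2), an evaluation will examine the current practice of CHWs". It also sets the purpose: "The objective is to describe differences in practice between the two arms of the trial". The indicators drawn from interviews, observation and programme records are to be analysed "with the primary comparison being between the two intervention arms".

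Two items in the records review carry a time window:
- Supervisory visits in both directions between CHWs and their supervisors, with the tools and feedback used, are taken for the "previous month (May 2011 – AFG Calendar").
- Activity counts are defined as "Number of CHW activities per month for each HP attached to our trial clinics over the trial length".

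On the trial calendar, section 2.5.3 refers to balance data collected "over the same study period i.e. July to December", and section 2.5.1 states: "The second phase of the trial will be initiated in Feb 2012".

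Section 2.5.7 says that the routine HMIS records will allow changes in practice to be assessed by "identifying changes in the number of each type of consultation". Section 2.6.2 lists the number of patients attended by CHWs, and the type of attendance, as a secondary outcome. Section 2.8.2 tabulates malaria, URTI and diarrhoea treatments for every study clinic for July to September 2010.

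**The concern.** An evaluation held at the end of a phase to compare arms needs records from that phase. A fixed calendar month before the trial cannot supply them, and it is not the month before either evaluation. If field staff follow the text, they will abstract the same pre-trial month for both evaluations. Any arm difference found would be a chance baseline difference, but it could be reported as a feature of the intervention.

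This matters most in Phase II. Section 2.5.1 says that the national plan behind Arm 2 contains no additional support, whereas Arm 3 adds regular support and quality assurance. How often CHWs were supervised, and with what tools, is a natural explanatory variable for that comparison.

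The attendance outcome raises a smaller question. Clinic workload varies widely and the protocol already holds a pre-trial value for each clinic, but the activity-count item covers the trial period only.

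**Working it through.** **Supervision window: dates side by side**

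| Event | Date | Source |
| --- | --- | --- |
| Month fixed for supervision records | May 2011 | 2.4 |
| Phase I months | July to December; 2011 inferred from the September 2011 draft date and the February 2012 start of Phase II | 2.5.3, 2.5.1 |
| Phase II start | February 2012 | 2.5.1 |

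- May to July 2011: 2 months before Phase I starts.
- May to December 2011: 7 months before Phase I ends, when the first evaluation is due.
- May 2011 to February 2012: 9 months before Phase II starts. This step does not depend on the inferred year.

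In May 2011 neither arm of either phase had received its intervention, so the between-arm difference in these records is a baseline difference. Calling it the previous month would be correct only for an evaluation held in June 2011, and section 2.4 describes none.

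**Attendance: 2010 counts under the actual Phase I allocation**

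Inputs are the clinic counts in section 2.8.2 and the allocation in section 2.5.5 (Tables 2 and 3).

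All three conditions:
- No RDT: 615 + 1394 + 129 + 451 + 867 + 1315 + 657 + 679 + 139 + 650 + 1081 = 7,977.
- RDT: 1459 + 524 + 250 + 452 + 933 + 1144 + 251 + 1014 + 809 + 85 + 821 = 7,742.
- Check: 7,977 + 7,742 = 15,719, the protocol's grand total. The arms differ by 235, about 3%.

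Malaria treatments:
- No RDT: 3 + 3 + 2 + 63 + 216 + 158 + 6 + 174 + 52 + 4 + 220 = 901.
- RDT: 450 + 10 + 45 + 2 + 310 + 0 + 17 + 382 + 189 + 0 + 212 = 1,617.
- Check: 901 + 1,617 = 2,518, the protocol's malaria total.
- Ratio: 1617/901 = 1.8. Share of treatments: 901/7977 = 11.3% against 1617/7742 = 20.9%.

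Spread between clinics: 1459/85 = 17.2-fold in clinic totals. Per health post it runs from 139/13 = 10.7 (Rodat) to 1394/7 = 199 (AngorBagh), 18.6-fold.

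Overall workload is therefore balanced. That is to be expected, because the allocation was restricted on a sample size weighted by the three conditions combined. Malaria case mix was not a restriction factor, and it was uneven before any RDT was issued under the trial.

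**The case against.** Four points can be made on the other side.

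1. **The date may be a slip in an otherwise relative window.** Previous month is a sensible relative definition, and only the parenthesis fixes it wrongly. That is fair, but the parenthesis is the operative instruction, and it conflicts with the evaluation's timing and purpose. It needs correcting whatever its origin.

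2. **Other sources cover supervision.** Section 2.4 plans interviews with CHWs and supervisors, and focus groups on supervisory structures. Annex 1 asks how often the CHW went to the clinic in the last week. This stands: a reader might infer that the evaluation can show nothing about supervision, and the protocol does not support that. These sources are mainly qualitative, however, and Annex 1 has no item on supervisor visits, tools or feedback. It is also fair that the text does not say Arm 3's regular support is delivered through supervisory visits, so that link is inferred.

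3. **Activity data are adequate for the stated aim.** A reader might infer that changes in CHW activity cannot be shown, or that only trial-period data exist. Neither is right. Monthly counts by randomised arm are a valid comparison without a baseline. Pre-trial activity data are also planned or held: time per activity before and during the trial (2.4), the Annex 1 form with previous-week counts completed at the start of the pre-study period (2.3), and the 2010 reports (2.8.2). What remains is a matter of precision and chance imbalance.

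4. **Adjustment belongs to the analysis plan, which section 2.8.4 defers.** This also stands. The 17-fold spread is between clinics, not arms, and the restricted randomisation balanced the totals. Adjustment is therefore offered as an improvement and not as the correction of an error.

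**Conclusion.** The supervision-record window is wrong as written. A month before both phases cannot serve an end-of-phase comparison of arms, so this item can show only pre-intervention differences. For Phase I the conclusion assumes that July to December means 2011; for Phase II it needs no such assumption. The reference to an Afghan calendar beside a Gregorian month is unclear, but a month corresponding to May 2011 is pre-trial under the same reading. The consequence is confined to one quantitative item of the process evaluation. Supervision is neither the primary outcome nor a listed secondary outcome.

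The attendance point is an optional gain. Trial-period counts remain valid, but a 1.8-fold difference in 2010 malaria treatments between the Phase I arms, together with the spread between clinics, makes adjustment worthwhile when the data are already in hand. No comparable figure can be given for Phase II, whose allocation is not in the protocol.

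A reader might also think of answering the objective on the CHW role in treating fever from the 2010 records. They cannot serve for that, because the table has no fever category.

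**What to change.** **Correction.** In section 2.4, define the window for supervisory visits as the last full month, or all months, of the phase being evaluated, and state it separately for Phase I and Phase II. Keep May 2011 only as a labelled baseline, and say which calendar the month refers to. The cost is a wording change and some further abstraction of programme records.

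**Improvement.** For the secondary outcome on number of patients attended and type of attendance, state that the comparison between arms will be adjusted for each clinic's July-September 2010 counts of malaria, URTI and diarrhoea treatments. This needs no new patients or procedures. The cost is a little extra analysis. The baseline is limited: it covers three months and three treatment categories, matches only part of the July-December period, and does not cover the February start of Phase II.
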